## Interventions

### Arm 1

Radiotherapy for patients in the standard arm should follow the principles of palliative radiotherapy as per the individual institution, with the goal of alleviating symptoms or preventing imminent complications. Patients in this arm should not receive stereotactic doses or radiotherapy boosts.

Treatment recommendations for patients in Arm 1 are as follows: For brain metastases, whole brain radiotherapy (i.e. 20 Gy in 5 fractions, 30 Gy in 10 fractions); for lung metastases, palliative radiotherapy as per 2011 consensus guidelines (i.e. 8 Gy in 1 fraction, 20 Gy in 5 fractions, 30 Gy in 10 fractions)[15]; for bone metastases, palliative radiotherapy as per 2011 consensus guidelines (i.e. 8 Gy in 1 fraction (most common), 20 Gy in 5 fractions, 30 Gy in 10 fractions)[16]; for liver metastases, 20 Gy in 5 fractions if standard institutional practice.

For Arm 1, Treatment planning is to be done using CT simulation or conventional simulation (fluoroscopy) as per individual institutional practice. Simple beam arrangements, such as parallel opposed beams, are favored wherever possible.

### Arm 2

For Arm 2, all treatments in this study are based on current protocols in clinical use at the LRCP and VUmc for treatment of lung [17], liver [18], brain [19,20], and spinal column [21] metastases. The guiding principle for radiotherapy is to achieve disease control but to minimize any potential adverse impact on quality of life. Concurrent chemotherapy or targeted therapy at the time of radiotherapy is not permitted within the 4 weeks prior to SABR. Hormone therapy is permitted.

Doses and fractionations by tumor site are shown in Table 1. Treatment will be setup using reproducible positioning, verified using an on-line protocol, for all patients in this study. Immobilization may include a custom immobilization device, such as thermoplastic shell or Vac-lok^TM^ bag, as per individual institutional practice when delivering SABR. Some centers do not use immobilization devices and have demonstrated high degrees of accuracy; this is acceptable in this study.

**Table 1 T1:** Dose and fractionations by site

**Tumor Location**	**Description**	**Total Dose (Gy)**	**Number of fractions**	**Dose per fraction (Gy)**	**Frequency**
**Lung**	Tumors 3 cm or less surrounded by lung parenchyma	54	3	18	Every second day
	Abutting chest wall or >3 cm	55	5	11	Every second day
	Within 2 cm of mediastinum or brachial plexus	60	8*	7.5	Every second day
**Bone**	Any bone except femur	35 Gy	5	7	Daily
	Vertebral body: additional options	16-20 Gy *OR*	1	16-20	Single dose
		30 Gy	3	10	Every second day
**Brain Metastases**	If whole brain treated, then simultaneous boost to each lesion	40 Gy to metastases 20 Gy whole brain (optional)	5	8 Gy to lesion 4 Gy WBRT	Daily
**Liver**	LRCP site: Dose is based on calculated normal tissue probability of <5%				Every second day
	Other sites	45-60	3-8	7.5-15	Every second day
**Adrenal**		60 Gy	8	7.5	Every second day

*If esophageal dose constraints cannot be met, 12 fractions should be used.

All patients in Arm 2 will undergo planning CT simulation. 4-dimensional CT will be used for tumors in the lungs or liver. Axial CT images will be obtained throughout the region of interest. For all lesions, the gross tumor volume (GTV) will be defined as the visible tumor on CT and/or MRI imaging +/- PET. No additional margin will be added for microscopic spread of disease, consistent with current protocols (i.e. Clinical Target Volume [CTV] = GTV). For vertebral lesions, the entire vertebral body may be considered the CTV, as per institutional practice. A Planning Target Volume (PTV) margin of 2-5 mm will be added depending on site of disease, immobilization, and institutional set-up accuracy: 2 mm margins may be used for spinal stereotactic treatments, 2 mm for brain tumors, and 5 mm for other sites. Organs at risk visible in the planning CT scan will be contoured. Constraints for 1-, 3- and 5-fraction regimens are taken from Timmerman *et al.* 2008 [22], whereas equivalent doses were calculated for other fractionation schemes.

For spinal lesions, a pre-treatment MRI is required to assess the extent of disease and position of the cord. This must be fused with the planning CT scan. A Planning Organ at Risk Volume (PRV) expansion of 2 mm will be added to the spinal cord, and dose constraints for the spinal cord apply to this PRV.

It is strongly recommended that dose constraints not be exceeded. If a dose constraint cannot be achieved due to overlap of the target with an organ at risk, the fractionation can be increased or the target coverage compromised in order to meet the constraint. It is strongly recommended that in cases where the target coverage is compromised in order to meet the constraint, the mean dose delivered to the GTV should be at least 80% of the nominal dose in Table 1. All such cases of dose reduction or target coverage compromise must be approved by the local PI prior to treatment. For vertebral tumors, an adequate PRV of 2 mm must be added to the spinal cord, and the dose constraints apply to this PRV.

For lung tumors, doses are prescribed to approximately the 80% isodose line surrounding the PTV, resulting in a hotspot of 120-140%; the latter should fall within the GTV. 95% of the PTV should be covered by the prescription dose, and 99% of the PTV should be covered by 90% of the prescription dose.

For other tumor sites, doses are prescribed to approximately the 100% isodose level and 95% of the PTV should receive 95% of the prescription dose. Doses will be corrected for tissue inhomogeneity. Several non-overlapping 6/10 MV beams (on the order of 7-11 beams) or 1-2 VMAT arcs combined possibly with a few non-coplanar beams is recommended. Non-coplanar beams can be used to reduce 50% isodose volume for un-gated treatments. Coplanar beams are recommended for respiratory-gated treatment.

For lung or liver metastases, each metastasis can be treated with a separate isocenter if metastases are well-separated. Since most metastases are treated every other day (Table 1), when two metastases are treated, these can be done on alternating days to reduce the daily time required on the linear accelerator (e.g. Monday/Wed/Friday for one target, and Tues/Thurs/Mon for another). For brain metastases, all the metastases should be treated at the same time. For bone metastases, if multiple metastases can be imaged and localized at the same time, they can be treated at the same time, otherwise, they can be treated on alternate days.

The sequencing of tumor sites is at the discretion of individual physicians, but in general should begin with the brain, due to risks associated with progression, followed thereafter by liver, lung, and bone.

### Quality assurance for centres joining study

Prior to opening the study, each participating research centre will be required to send to one of the Principal Investigators a mock treatment plan for the anatomic sites that will be treated (e.g. lung, brain, liver, adrenal), to ensure that the treatment plans are designed in compliance with the protocol. The principal investigators will provide pertinent CT datasets. Each participating research centre can choose which tumor sites will be treated at their individual centre (i.e. some centres may only choose to treat a subset of the eligible metastatic sites).

### Chemotherapy

Patients treated with prior chemotherapy are eligible for this study, however, no chemotherapy agents (cytotoxic, or molecularly targeted agents) are allowed within the period of time commencing 4 weeks prior to radiotherapy (conventional or SABR) lasting until 2 weeks after the last fraction. Hormonal therapy is allowed**.** Use of chemotherapy schemes containing potent enhancers of radiation damage (e.g. gemcitabine, adriamycin) are discouraged within the first month after SABR.

### Further radiotherapy for progressive disease at new metastatic sites

Patients in Arm 1 who develop new, untreated metastatic deposits can receive palliative radiotherapy for any new such sites of progression. Patients in Arm 2 who develop new, untreated metastatic deposits should be considered for SABR at those sites, if such deposits can be treated safely with SABR, and if the treating institution offers SABR for that body site. If SABR is not possible, then palliative RT can be delivered if indicated.

### Follow-up

Patients will be seen every three months post-randomization for the first two years, and every six months until 5 years after treatment (Table 2). At each visit, a history and physical examination will be conducted by the oncologist, and CTC-AE toxicities recorded. The FACT-G Quality of life questionnaire is to be completed at each visit.

CT head, chest, abdomen and pelvis, and bone scans will be repeated at 3 and 6 months, then every six months. Patients randomized to Arm 2 will be considered SABR for salvage if new sites of disease develop. Additional Imaging or laboratory investigations should be carried out at the discretion of the oncologist, based on findings in the history or physical, and additional treatment (e.g. further chemotherapy) is at the discretion of the oncologists.

### Measurement of response

Overall survival will be measured as time until death from any cause, and progression-free survival as time to either progression or death, whichever occurs first. Lesion response will be evaluated in this study using the international criteria proposed by the Response Evaluation Criteria in Solid Tumors (RECIST) Committee (http://ctep.info.nih.gov/guidelines/recist.html). The sum of the longest diameter (LD) for all target lesions will be calculated and reported as the baseline sum LD. The baseline sum LD will be used as reference by which to characterize the objective tumor response.

## Statistical analysis

### Sample size

This study will employ a randomized phase II design, to conduct a preliminary and non-definitive randomized comparison between the control and experimental arms. The study will aim to detect a signal in improved overall survival that would be used to design a phase III study to definitely compare survival outcomes between the two groups. The study will therefore be designed with alpha = 0.20 and beta = 0.20 (as recommended for phase II randomized studies [23]). It is estimated that the median survival of the control group after randomization in this study will be 9 months.

There will be a 1:2 randomization between Arm 1 and Arm 2. In order to detect a 6-month improvement in median survival from 9 months to 15 months with SABR, a total of 93 patients (31 in Arm 1 and 62 in Arm 2) will be needed. Assuming a 5% rate of loss to follow-up, a total of 99 patients will be accrued (33 in Arm 1 and 66 in Arm 2). The study projects accrual over 48 months with 12 months of additional follow-up. Accrual targets are as follows: 20 patients in year 1, and 25-30 patients in years 2, 3, and 4.

### Data analysis

Patients will be analyzed in the groups to which they are assigned (intention-to-treat).

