**Methods:**

After stratification by the number of metastases (1-3 vs. 4-5), patients will be randomized between Arm 1: current standard of care treatment, and Arm 2: standard of care treatment + SABR to all sites of known disease. Patients will be randomized in a 1:2 ratio to Arm 1:Arm 2, respectively. For patients receiving SABR, radiotherapy dose and fractionation depends on the site of metastasis and the proximity to critical normal structures. This study aims to accrue a total of 99 patients within four years. The primary endpoint is overall survival, and secondary endpoints include quality of life, toxicity, progression-free survival, lesion control rate, and number of cycles of further chemotherapy/systemic therapy.

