**Figure 1 F1:**
[figure not shown]
** Study design.** Patients with be randomized in a 1:2 ratio between Arm 1 (Standard of care) vs. Arm 2 (SABR).

The randomized phase II design is required for 3 reasons: First, the randomization will provide an appropriate control group to serve as a comparator for the experimental arm. Historical or contemporaneous non-randomized controls would not be appropriate due to the multitude of biases that could be introduced by patient selection and other confounders. Second, a small sample size will allow for adequate power to assess for an early overall survival difference, quality of life, and to evaluate toxicity in the SABR arm. Third, the results will allow for a decision as to whether a multi-institutional phase III trial is warranted, and inform the design of such a trial.

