#### Secondary endpoints

· Quality of life

· Assessed with the Functional Assessment of Cancer Therapy: General (FACT-G)

· Toxicity

· Assessed by the National Cancer Institute Common Toxicity Criteria (NCI-CTC) version 4 for each organ treated (e.g. liver, lung, bone)]

· Progression-free survival

· Time from randomization to disease progression at any site or death

· Lesional control rate

· Number of cycles of further chemotherapy/systemic therapy

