#### Secondary endpoints

Quality of life at 6 months will be measured using FACT-G scores, with differences between groups tested using the Student’s *t*-test. Differences in rates of grade 2 or higher toxicity between groups will be tested using the Fisher’s Exact Test. Differences in progression free survival will be tested using the stratified log-rank test. Differences in the number of cycles of further chemotherapy/systemic therapy will be tested using the Student’s *t*-test.

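### The unqualified intention-to-treat rule also governs the toxicity test, so non-receipt of SABR in Arm 2, or SABR given in Arm 1, dilutes the SABR toxicity contrast toward no difference

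*Protocol article*

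**What the plan says.** In the Protocol article, the Data analysis section begins with a single sentence on populations: "Patients will be analyzed in the groups to which they are assigned (intention-to-treat". It stands above both the primary and the secondary endpoint paragraphs and excepts no endpoint. The Secondary endpoints paragraph below it states: "Differences in rates of grade 2 or higher toxicity between groups will be tested", using Fisher's exact test. No as-treated or safety population is named.

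Other passages bear on how the rule works for toxicity:

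- Methods/design, in the text below Figure 1, lists among the reasons for the design "to evaluate toxicity in the SABR arm".
- Secondary endpoints under Objectives grades toxicity by NCI-CTC "version 4 for each organ treated".
- Follow-up collects toxicity from everyone: "At each visit, a history and physical examination will be conducted by the oncologist, and CTC-AE toxicities recorded".
- The abstract describes Arm 2 as "standard of care treatment + SABR to all sites of known disease", so an Arm 2 patient who misses SABR still has standard care.
- Interventions, Arm 1, bars crossover: "Patients in this arm should not receive stereotactic doses or radiotherapy boosts".

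**The concern.** Analysis by assignment is the right default for survival. Non-adherence there moves the result toward no difference, which makes a claim of benefit harder to reach. For harm the same movement makes SABR look safer than it is.

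The trial is meant to describe SABR toxicity and to inform a phase III decision, so the figure of most use is the rate among patients who received SABR. The by-assignment rate in Arm 2 mixes that with the rate in patients who never started it.

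Some non-receipt is possible because several steps follow randomization. The planning scan ("All patients in Arm 2 will undergo planning CT simulation"), the checks of dose to organs at risk and the discussion at quality-assurance rounds are all described for Arm 2. Staging may be up to 12 weeks old at randomization, and the assumed control median survival is 9 months, so some patients may deteriorate before SABR begins.

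**Working it through.** **Plan's own figures.** The article gives no rates, alpha or power for the toxicity test, so there is no stated toxicity figure to reproduce. The survival sample size supplies the denominators, and it does reproduce. Take exponential survival with medians 9 and 15 months (hazard ratio 0.60), 48 months' accrual plus 12 months' follow-up, and two-sided alpha 0.20. The event probabilities are then 0.895 and 0.769. The control-arm size is (1.282 + 0.842)² × [1/0.895 + 1/(2 × 0.769)] / (ln 0.60)² = 30.5, rounded to 31. This gives 31 + 62 = 93. With 5% loss, 31/0.95 = 32.6 and 62/0.95 = 65.3, so 33 + 66 = 99.

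**Inputs for the check**

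- From the article (Sample size): 33 patients in Arm 1 and 66 in Arm 2.
- Assumed: true grade 2+ rates t = 30% with SABR and c = 10% without.
- Assumed: share q of Arm 2 never starting SABR = 5%, 10%, 15%.
- Assumed: test level 0.05 or 0.20, two-sided.

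**Formula.** If untreated Arm 2 patients have the no-SABR rate, the Arm 2 rate by assignment is t(1 − q) + cq = t − q(t − c). If a share r of Arm 1 receives SABR, the Arm 1 rate is c + r(t − c). The observed difference is therefore (t − c)(1 − q − r). The figures below set r = 0, because the article bars SABR in Arm 1.

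**Rates**

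- q = 5%: 30 − 0.05 × 20 = 29%
- q = 10%: 30 − 0.10 × 20 = 28%
- q = 15%: 30 − 0.15 × 20 = 27%

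**Power.** This is exact two-sided Fisher power in the direction of more toxicity with SABR, by full enumeration of both binomials. By assignment the comparison is 33 vs 66. Treated-only keeps the 33 controls and the Arm 2 patients who started SABR (66 − 3 = 63, 66 − 7 = 59, 66 − 10 = 56). With q = 0, power is 60.2% at 0.05 and 82.5% at 0.20.

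| q | By assignment, 0.05 | Treated-only, 0.05 | By assignment, 0.20 | Treated-only, 0.20 |
|---|---|---|---|---|
| 5% | 56.1% | 58.7% | 79.8% | 81.0% |
| 10% | 51.9% | 56.5% | 76.9% | 80.6% |
| 15% | 47.6% | 57.3% | 73.6% | 82.5% |

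The treated-only column does not fall steadily as n shrinks. That is the discreteness of Fisher's test, and it flatters the contrast at q = 15%. The shift in the rate, q(t − c), is the steadier measure.

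**The case against.** **The toxicity-free reading.** A reader might infer, from the endpoint being graded by treated organ, that an unirradiated Arm 2 patient is scored as free of toxicity. The dilution would then be qt. The Arm 2 rate would read 28.5%, 27.0% and 25.5%, and power at 0.05 would be 54.0%, 47.6% and 41.1%. The text does not support this. Toxicity is recorded at every visit without regard to treatment received, and Arm 2 patients also have standard care. The same reading would also score unirradiated controls as zero. The dilution is q(t − c).

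**Non-receipt may be rare.** A reader might also infer that the plan makes non-receipt likely. The inclusion criteria require that all sites can be treated safely and that tumor board or departmental rounds agree to entry. The exclusion criteria remove patients whose active sites cannot all be treated. When a dose constraint cannot be met, the article provides for changing fractionation or coverage. The chemotherapy-free interval applies to conventional radiotherapy as well as SABR. Non-receipt remains possible, but nothing in the article says it will be common.

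**By-assignment toxicity is a valid comparison.** It compares the assigned strategies, keeps the randomization and fits an objective worded around a treatment program. The data safety monitoring committee also reviews every grade 3–5 case. This stands: the by-assignment comparison belongs in the report. The weakness is that it is the only one stated, and the committee's case review does not replace the final grade 2+ comparison.

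**A condensed article.** A safety population may be defined in the full protocol or analysis plan, so its absence here is not an error. The point rests on the rule that is stated, which as worded would contradict such a population.

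**Conclusion.** The point holds as a dilution. The intention-to-treat rule as written governs the toxicity test, and any non-receipt of SABR in Arm 2 or SABR given in Arm 1 narrows the observed difference by the factor (1 − q − r).

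Under the assumed 30% and 10% rates, the Arm 2 rate is understated by 1, 2 or 3 percentage points at 5%, 10% or 15% non-receipt. Against the treated-only comparison, the power cost at 0.05 is 58.7 − 56.1 = 2.6, 56.5 − 51.9 = 4.6 and 57.3 − 47.6 = 9.7 points. At 0.20 it is 81.0 − 79.8 = 1.2, 80.6 − 76.9 = 3.7 and 82.5 − 73.6 = 8.9 points.

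At about 5% non-receipt the effect is small, and this is a secondary test in a trial described as preliminary. The direction is certain whenever t exceeds c. The size rests on rates that the article does not give. The documents do not support saying that untreated patients are counted as free of toxicity, or that non-receipt is likely.

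**What to change.** Limit the intention-to-treat sentence to the efficacy and quality-of-life endpoints, and add a sentence for toxicity:

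- The main toxicity comparison is by treatment actually received. Every patient who received at least one SABR fraction is counted in the SABR group, whatever the assigned arm. All others are counted in the no-SABR group.
- The by-assignment comparison is reported as supportive.
- The number of Arm 2 patients who never received SABR is stated.

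This grouping discards no one. Dropping untreated Arm 2 patients and any control given SABR would be a per-protocol exclusion, and it would lose the SABR toxicity of any crossover patient. The treated-only figures above measure the dilution and are not the power of this comparison, which would have 36 vs 63, 40 vs 59 or 43 vs 56 patients in the three scenarios.

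The cost is a sentence or two in the analysis section and no new data. The downside is that a comparison by treatment received is not strictly randomized, since patients who never start SABR may differ in prognosis and background toxicity. That is why the by-assignment table should stay beside it.

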#### Primary endpoint

Survival will be calculated using the Kaplan-Meier method with differences compared using the stratified log-rank test. Pre-planned subgroup analysis will occur based on stratification variables. A Cox multivariable regression analysis will be used to determine baseline factors predictive of survival and allow for assessment of time to failure data important in this patient group.

#### Secondary endpoints

Quality of life at 6 months will be measured using FACT-G scores, with differences between groups tested using the Student’s *t*-test. Differences in rates of grade 2 or higher toxicity between groups will be tested using the Fisher’s Exact Test. Differences in progression free survival will be tested using the stratified log-rank test. Differences in the number of cycles of further chemotherapy/systemic therapy will be tested using the Student’s *t*-test.

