### Evaluation and randomization

Prior to randomization, a complete history and physical examination by the treating radiation oncologist is required. Histologically confirmation of malignancy is required, with metastatic disease detected on imaging. Biopsy of metastasis is preferred, but not required.

Patients must be restaged within 12 weeks prior to randomization, including brain CT or MRI imaging (for tumor sites with propensity for brain metastasis); and CT neck/chest/abdomen/pelvis with bone scan. PET-CT is only required for specific evidence-based indications, as defined by the Ontario Health Insurance Program, and in such cases the CT neck/chest/abdomen/pelvis and bone scan are not required. For other indications, at the discretion of the treating oncologists, PET-CT scans may be done but are not required. MRI spine is required for patients with vertebral or paraspinal metastases.

Patients with liver metastases are also required to have adequate liver function tests (AST, ALT, GGT, alkaline phosphatase). A negative pregnancy test is required for women of child-bearing age.

The study will employ a 1:2 randomization between Arm 1:Arm 2 (Figure 1). The sample size allows for one stratification factor at randomization: number of metastatic sites (1-3 vs. 4-5). Randomization will occur in permuted blocks of nine.

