### Data safety monitoring committee

The DSMC will meet annually after study initiation and after 50 patients are accrued to review toxicity outcomes. If any grade 3-5 toxicity is reported, the DSMC will review the case notes to determine if such toxicity is related to treatment. If the DSMC deems that toxicity rates are excessive (>25% grade 3 toxicity, or >5% grade 4 or 5 toxicity), then the DSMC can, at its discretion, recommend cessation of the trial, dose adjustment, or exclusion of certain treatment sites that are deemed as high-risk for complications.

The DSMC will conduct one interim analysis once 50 patients are accrued. For this analysis, the DSMC will be blinded to the identity of each treatment arm, but OS data will be presented for each arm. The DSMC will recommend stopping the trial if there is an OS difference that is statistically significant with a threshold of p < 0.001 using the log-rank test. Furthermore, if the median OS among all patients is substantially different than estimated in the sample size calculation, the DSMC can recommend increasing or decreasing the target accrual in order to maintain statistical power.

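### Minor, low-cost improvement: the randomization stratum (1-3 vs 4-5 metastases) is used in the final OS and PFS tests but not in the toxicity, systemic-therapy and FACT-G tests, nor named in the interim OS rule

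*Protocol article*

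**What the plan says.** **Allocation.** Under Evaluation and randomization, the protocol article states "The sample size allows for one stratification factor at randomization: number of metastatic sites (1-3 vs. 4-5", and then "Randomization will occur in permuted blocks of nine". The ratio is fixed under Sample size: "There will be a 1:2 randomization between Arm 1 and Arm 2".

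**Tests that use the factor.** The final overall survival (OS) comparison is a stratified log-rank test (Data analysis, Primary endpoint). The next section treats progression-free survival (PFS) the same way: "Differences in progression free survival will be tested using the stratified log-rank test".

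**Tests that do not.** The same Secondary endpoints paragraph reads "Differences in rates of grade 2 or higher toxicity between groups will be tested using the" and goes on to name Fisher's exact test. Student's t-test is named for the number of cycles of later systemic therapy and for FACT-G at 6 months. The stopping rule under Data safety monitoring committee requires an OS difference that is "statistically significant with a threshold of p < 0.001 using the log-rank test", with no mention of stratification.

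**Operating characteristics.** The only error rates given are for OS: "The study will therefore be designed with alpha = 0.20 and beta = 0.20". No alpha, power or sample size is attached to any secondary test.

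**The concern.** Permuted blocks within strata hold each stratum close to 1:2. That removes between-stratum variation from the arm comparison. A test that ignores the stratum still counts this variation as noise, so its standard error is too large whenever the stratum predicts the outcome. The test then runs below its nominal level and gives up power.

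Toxicity is the natural place to look. Arm 2 irradiates every known site, so the stratum largely sets how many sites are treated there. For a harm comparison a conservative test is not automatically the safe choice, because it makes a real excess easier to miss. Quality of life is part of the stated objective, so the FACT-G test matters too. At the interim, a stopping rule should leave no doubt about which p-value is meant, since the stratified and unstratified tests can differ on the same data.

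**Working it through.** **1. The plan's own figure.** The design statement is "In order to detect a 6-month improvement in median survival from 9 months to 15 months with SABR, a total of 93 patients". With exponential survival the hazard ratio is 9/15 = 0.60. Taking alpha 0.20 as two-sided, the Schoenfeld formula gives (1.2816 + 0.8416)² / [(1/3)(2/3)(ln 0.60)²] = 4.508 / 0.05799 = 77.7, or 78 events. With 48 months of uniform accrual plus 12 months of follow-up, the chance of an observed death is 0.895 in Arm 1 and 0.769 in Arm 2, a weighted average of 0.811. Then 77.7 / 0.811 = 95.8 patients. The Lachin-Foulkes formula gives 94.5, and power at 93 patients is 79.1%. The stated 93 is therefore reproduced. One-sided alpha 0.20 would need only about 60 to 61. For losses, 93 / 0.95 = 97.9, and 99 is the next multiple of three. Nothing below changes this sample size.

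**2. Why ignoring the stratum is conservative.** As an assumed example, let 25% of patients have 4-5 metastases, with toxicity 15% (1-3) and 50% (4-5) in both arms.
- Overall risk: 0.75 × 0.15 + 0.25 × 0.50 = 0.2375. Variance used by an unstratified test: 0.2375 × 0.7625 = 0.1811.
- Variance within strata: 0.75 × 0.1275 + 0.25 × 0.25 = 0.1581.
- Ratio 0.873, square root 0.934. The effective critical value is 1.96 / 0.934 = 2.10, so the true two-sided level is about 3.6%, not 5%.

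Simulation of this case gave 2.5% (Fisher), 3.4% (unstratified score test) and 4.7% (CMH). The level falls; it does not rise.

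**3. Toxicity power.** Inputs from the protocol: 99 patients, 1:2, blocks of nine within stratum. Assumptions, because the protocol gives none: two-sided 0.05; 10%, 30% or 50% of patients in the 4-5 stratum; 10% control risk in the 1-3 stratum; 0, 15 or 30 points more risk in the 4-5 stratum, in both arms; 20 or 25 points more with SABR. CMH sums observed minus expected Arm 2 events over strata, squares the sum, and divides by the summed hypergeometric variances.

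| Added risk in 4-5 stratum | Stratified exact minus Fisher | CMH minus Fisher |
|---|---|---|
| 0 points | about 0 | about 3 to 5 |
| 15 points | about 0 to 1 | about 4 to 6 |
| 30 points | about 2 to 4.5 | about 5 to 8.5 |

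The entries are percentage points of power. With no arm difference, the true level was 2.3-3.3% for Fisher, 2.4-4.0% for the stratified exact test and 3.7-5.4% for CMH. The first row isolates Fisher's conservatism, and the middle column isolates the stratum.

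Another scenario splits the gain directly. With 25% in the 4-5 stratum, toxicity 10% vs 30% (1-3) and 30% vs 60% (4-5), power was 62.6% (Fisher), 66.7% (unstratified score) and 69.7% (CMH). Leaving Fisher's test gives 4.1 points and the stratum 3.0. If the stratum acts only in Arm 2 (10% vs 30% and 10% vs 50%), it adds only 0.2 to 0.4 point.

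**4. The t-tests.** Assume an arm difference of 0.6 SD. Leaving the stratum out costs nothing if it has no effect, 0.5 to 1.7 points of power if it shifts the outcome by 0.5 SD, and 2 to 8 points at 1 SD. The true level stays at 4.4-5.2%, except for a 1 SD shift with 30-50% of patients in the 4-5 stratum, where it falls to about 3%.

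**5. The interim test.** At 50 patients about 21 deaths are expected under a hazard ratio of 0.60, and about 25 to 26 under no difference. Stratum hazard ratios of 1 to 2.5 were assumed. The chance of p < 0.001 under no difference is 0.08-0.19% unstratified and 0.12-0.20% stratified. Under 0.60 it is 1.7-3.0% and 2.2-2.6%. Within any one scenario the two differ by at most about 0.5 point, in either direction.

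**The case against.** The case against acting is substantial, and most of it stands.

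- **Most of the toxicity gain is not about stratification.** Some 3 to 5 points come from replacing an exact test. Choosing between a guaranteed level and a few points of power, with about 33 vs 66 patients, is a defensible judgement. This limits the size of the point.
- **The mechanism is weaker than it looks.** Arm 1 receives symptom-directed palliative radiotherapy, so control-arm toxicity need not rise much with the number of metastases. If it does not, the stratum contributes almost nothing. This stands too.
- **Patient safety does not hang on this p-value.** The monitoring committee reviews toxicity annually and after 50 patients, examines the cases of grade 3-5 events, and has rate thresholds.
- **Adjustment of secondary endpoints is often settled in an analysis plan, which is not shown, and the interim wording may be shorthand for the stratified test.** Both are possible. But the article does not leave the tests open: it names each one, and one paragraph writes stratified for PFS and then names tests without the factor. That inconsistency remains.

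A reader might infer that ignoring the stratum distorts the error rates, or that these tests miss a power the design promised. The documents support neither reading. False positives do not rise, no power or level is promised for any secondary test, and the effect depends on a prognostic strength that the article does not give.

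**Conclusion.** A real inconsistency with small consequences. The toxicity, systemic-therapy and FACT-G tests, and the interim rule as worded, do not use the stratum, while the final OS and PFS tests do. The affected tests remain valid at or below nominal level and may lose power.

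For toxicity, moving to CMH gains about 3 to 8 points, of which about 0 to 4 belong to the stratum. For the t-tests the loss runs from nothing to about 8 points, the upper end only if the stratum shifts the outcome by a full SD and is common. At the interim the matter is consistency alone. These sizes rest on the assumed stratum shares, risks and two-sided 5% level; the only alpha stated in the article is 0.20, for OS. The trial presents itself as preliminary, which also argues for rating this as minor.

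**What to change.** - **Toxicity (Data analysis, Secondary endpoints):** replace Fisher's test with a CMH test stratified by number of metastases (1-3 vs 4-5), and report a stratified risk difference with 95% CI. If cells are sparse, use an exact stratified test, accepting that it gives up most of the gain in most of the scenarios above.
- **Cycles and FACT-G (same section):** include the stratum as a term in both comparisons.
- **Interim rule (Data safety monitoring committee):** name the stratified log-rank test, as in the final primary analysis.

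The cost is wording only. The stratum is recorded at randomization, and the sample size is unaffected. There are two small downsides: CMH does not guarantee its level exactly (up to 5.4-5.5% in the simulations), and a very small 4-5 stratum would contribute little.
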